### FFR INFORMED group

Within the FFR-INFORMED group, the baseline CMR scan is blinded. This scan is not used to guide further management but will provide valuable additional scientific data that will be used in analyses specific to the substudies (described below). All patients in this group are examined with invasive angiography, FFR is performed in all arteries > 2.5 mm with a diameter stenosis > 40%. FFR is attempted in all arteries up to a 99% stenosis, as long as patency is not compromised. Although this strategy differs from clinical practice, which tends to focus more on intermediate lesions, evidence from the FAME trial suggests that even in severe and mild stenosis the visual estimate can be inaccurate [17]. The cut-off of 40% was used to ensure that all stenoses in the intermediate group i.e 50 -70% were interrogated with the pressure wire. The results of invasive angiography and the FFR are used to guide further treatment. Any narrowing with an FFR of > 0.8 is regarded as not haemodynamically significant, whereas a narrowing with an FFR of ≤ 0.8 or a total occlusion is regarded as significant and revascularisation is indicated. The decision on the mode of revascularisation is left to the treating Cardiologist and depends on local practice. In the case of repeat revascularisation, when symptoms are ongoing, revascularisation will be guided according to either the FFR or CMR results depending on the group randomised.

### MR- INFORMED group

Within the MR-INFORMED group, further management is dictated by the results of the baseline CMR scan. A visual assessment of the significance of ischaemia and the territories involved is made (see investigation reporting below). Patients with significant perfusion defects are referred for angiography and revascularisation is guided by the ischaemic territories identified on the CMR scan in combination with the results of the angiogram. FFR should not be done in this group.

### Baseline and follow-up visits

All patients undergo a thorough cardiovascular risk assessment at baseline with measurement of blood pressure, glucose levels, body mass index, including measurement of waist circumference, full lipid profile, the completion of a health questionnaire (EQ-5D) and a 12 lead ECG. Symptomatic status is recorded by CCS and NYHA class. Medical therapy is optimised in all patients and the risk factor assessments are repeated at 6 and 12 months to assess the impact of medical therapy.

Furthermore, a 6 month follow-up CMR scan will be done in a subgroup of patients to assess for residual ischaemia, new scar formation and changes in left ventricular function and size after the initial therapy recommended after the baseline investigations. The result of this CMR scan will remain blinded.

### Optimal medical therapy

At baseline, 6 months and 12 months recommendations for therapy are made to the primary care physician in line with guidelines published by the Joint British Societies [18]. See Table 3 for the treatment targets.

**Table 3 T3:** Risk factor goals

**Risk Factor Goals**	
**Blood Pressure**	BP 130/80 mmHg
**Diabetes Mellitus**	Fasting or pre-prandial glucose of 4-6, or a HbA1C < 6.5%
**Lipids**	Total cholesterol less than 4 mmol/l or an LDL < 2.0 mmol/l
**Smoking**	Smoking cessation
**Weight**	BMI < 25

The goal of anti-hypertensive therapy is to achieve a blood pressure of less than 130/80 mmHg. The choice of anti-hypertensive therapy will be left to the treating physician.The aim of anti-lipid therapy is to achieve levels of LDL < 2 mmol/l and total cholesterol < 4 mmol/l. In the first instance, statin therapy will be initiated and then increased with the addition of a second agent if necessary. For patients with a BMI of > 25 kg/m^2^, the primary health care physicians are asked to refer the patient for dietary advice. Similarly, smokers are referred to the smoking cessation clinic. Recommendations for referral and for the continuation of therapy are made to the primary health care physician.

In patients without diabetes, who have a raised random glucose, the primary health care physician is asked to repeat a fasting glucose to assess for sustained hyperglycaemia, in which case the appropriate dietary advice and/or diabetic treatment should be instituted. In the case of diabetics with a raised blood sugar, the primary health care physician is asked to measure HbA1c and to ensure that the patients’ subsequent therapy is tailored to achieve a HbA1c of less than 6.5 mg/dl. All patients should be prescribed aspirin (clopidogrel if aspirin sensitive), statin therapy and an ACE Inhibitor [19].

### Investigations

#### CMR scanning

CMR imaging will be performed on 1.5 T scanners (various vendors); total scan duration will be approximately one hour. All images will be acquired using phased array surface coils during mild expiration and electrocardiographic triggering. Cine images will be acquired in the 4-, 3-, 2-chamber and contiguous short axis views using a steady state free precession (SSFP) sequence (Figure 2). For perfusion, a basal, midventricular, and apical short axis slice will be acquired during the first pass of 0.075 ml/kg of a 1-molar gadolinium based contrast agent injected with a power injector at a flow rate of 4mls/s. The exact details of the sequence will vary between different scanners used but will fulfill certain basic criteria, including high spatial resolution(< 3 mm x 3 mm), acquisition duration < 180 ms per slice, 90° saturation pre-pulse, fixed pre-pulse delay and dual bolus contrast injection allowing semi-quantitative and fully quantitative analysis [20]. Hyperaemia will be achieved by infusion of adenosine at 140mcg/kg/min for 3-4 minutes. If there is neither a heart rate increase > 10 bpm nor a systolic blood pressure drop > 10 mmHg from baseline nor symptoms the adenosine dose will be increased to 170 mcg/kg/min after 2 minutes and to a maximum dose of 210 mcg/kg/min [21]. All patients will be asked to avoid caffeine, but to continue with their normal medication for 12 hours prior to the scan. For the perfusion measurements, contrast agent will be injected at the third minute of adequate adenosine stress using a dual bolus method. A dose of 0.075 mmol/kg of a 1-molar gadolinium-chelate (Gadobutrol, Gadovist®, Bayer, Germany) will be injected for the main bolus preceded by the same volume of a 10% diluted contrast agent dose for a prebolus both flushed with 25 ml of saline. Rest perfusion imaging will be performed 10 min after stress perfusion to allow for clearance of most of the contrast agent.

**Figure 2 F2:**
[figure not shown]
**MR-INFORM cardiac magnetic resonance protocol.** After individual patient planning using survey scans, intravenous adenosine is given according to the protocol. First pass stress perfusion imaging is done during stress visualizing the first passage of a 0.75 mmol/kg contrast agent bolus through the myocardium. Short axis (SA) cine images are acquired. Rest perfusion images are acquired during an injection of a second bolus of 0.75 mmol/kg contrast agent. 10 minutes after an additional injection of 0.05 mmol/kg of contrast agent to increase the total dose of contrast agent to 0.2 mmol/kg is given. A modified Look-Locker inversion time scout is performed prior to late gadolinium enhancement imaging in short axis and long axis views. During the wait time after the last contrast agent injection long axis images in the 4 chamber, 3 chamber and the 2 chamber views are obtained.

Late enhancement imaging will then be carried out using an inversion recovery turbo gradient echo sequence.

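### The article gives the CMR contrast bolus as 0.075 mmol/kg in the methods text and 0.75 mmol/kg in the Figure 2 legend, and the legend's doses do not sum to its stated total

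*Protocol article*

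**What the plan says.** The CMR scanning section of the protocol article states the perfusion bolus twice. By volume, it speaks of the "first pass of 0.075 ml/kg of a 1-molar gadolinium based contrast agent". By amount, it says "A dose of 0.075 mmol/kg of a 1-molar gadolinium-chelate" is injected as the main bolus, "preceded by the same volume of a 10% diluted contrast agent dose for a prebolus". The prebolus is described where the text deals with injection under adenosine stress. The following sentence, on rest perfusion, gives no dose and does not mention a prebolus.

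The Figure 2 legend, headed as the trial's cardiac magnetic resonance protocol, goes through the same scan in order:

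- Stress imaging: "visualizing the first passage of a 0.75 mmol/kg contrast agent bolus through the myocardium".
- Rest imaging: "Rest perfusion images are acquired during an injection of a second bolus of 0.75 mmol/kg contrast agent".
- Before late enhancement: "an additional injection of 0.05 mmol/kg of contrast agent", given "to increase the total dose of contrast agent to 0.2 mmol/kg".

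The legend mentions no prebolus. The Patient population section says that all patients have the baseline stress perfusion scan, and Table 2 excludes a GFR below 30 ml/min.

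**The concern.** Two descriptions of one injection, in the same article, differ by a factor of ten. A reader who works from the legend and one who works from the text would take away different amounts. The legend cannot be read consistently even alone, because a single bolus at its stated size already exceeds the total it gives for the whole examination.

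The amount in question is a contrast dose given to every randomised patient in both arms, and a subgroup is scanned again at 6 months. Patients with reduced renal function are eligible down to the GFR limit. In the MR-INFORMED arm the scan decides who is referred for angiography, and the dual-bolus acquisition supports the quantitative perfusion substudy. An ambiguous bolus is therefore a possible safety matter, and possibly one for the quality of the perfusion reading, but only if it also appears in the documents from which sites work.

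**Working it through.** **Inputs**

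| Item | Value | Source |
|---|---|---|
| Bolus by volume | 0.075 ml/kg, 1-molar agent | CMR scanning |
| Bolus by amount | 0.075 mmol/kg | CMR scanning |
| Prebolus | same volume at 10% | CMR scanning |
| Stress bolus | 0.75 mmol/kg | Figure 2 legend |
| Rest bolus | 0.75 mmol/kg | Figure 2 legend |
| Additional injection | 0.05 mmol/kg | Figure 2 legend |
| Stated total | 0.2 mmol/kg | Figure 2 legend |

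**Step 1: is the scanning text consistent with itself?** A 1-molar agent holds 1 mmol per ml, so 0.075 ml/kg × 1 mmol/ml = 0.075 mmol/kg. The two expressions agree.

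**Step 2: reproduce the legend's total from the legend's own figures.** Total = stress bolus + rest bolus + additional injection = 0.75 + 0.75 + 0.05 = 1.55 mmol/kg. The stated total is 0.2 mmol/kg, and 1.55 / 0.2 = 7.75. The total is not reproduced.

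**Step 3: size of the conflict between text and legend.** 0.75 / 0.075 = 10.

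**Step 4: put the scanning text's bolus into the legend's sum.** 0.075 + 0.075 + 0.05 = 0.20 mmol/kg, which equals the stated total. Worked backwards, the total implies (0.2 − 0.05) / 2 = 0.075 mmol/kg per bolus.

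**Step 5: can the prebolus explain the gap?** The prebolus has the same volume at 10% strength, so it carries one tenth of the main bolus. The text does not say whether one is given at rest, so both counts are shown.

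| Main bolus (mmol/kg) | No prebolus | Counted once | Counted twice |
|---|---|---|---|
| 0.075 | 0.200 | 0.2075 | 0.215 |
| 0.75 | 1.55 | 1.625 | 1.70 |

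Counting the prebolus only moves the 0.75 sums further from 0.2. With 0.075 it adds 0.0075 to 0.015 mmol/kg, and both sums still round to 0.2 at the one decimal the legend uses.

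These sums show which printed figures agree with each other. They do not show which dose is intended.

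**The case against.** The strongest reply is that this is a slip in a published figure legend with no operational consequence. The scanning text gives the bolus in two agreeing forms, the legend's total is consistent with that text, and anyone comparing the two places sees the conflict at once. The Trial status section reports 235 patients already recruited at submission, so sites were scanning before the article appeared and must have had other instructions.

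Much of this stands, and it limits what may be concluded:

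- A reader might infer that sites hold the conflicting figure. The documents do not show that. The legend belongs to a journal article, and the full protocol and any imaging manual are not at hand. The training described under Perfusion analysis concerns image interpretation, not dosing.
- A reader might infer that doses differ between sites, and that perfusion readings therefore differ. Nothing supports this. The scanning text lets sequence details vary by scanner but names one bolus.
- A reader might infer that the stated total wrongly leaves out two preboluses, or 0.015 mmol/kg. The text describes a prebolus only in the context of stress, so the extra amount is 0.0075 to 0.015 mmol/kg under an assumption, and it is lost in rounding. This is an ambiguity about what the total includes, not a demonstrated error.
- A reader might infer from the arithmetic that the legend is the faulty place. A misplaced decimal there is plausible, but it remains an inference, and this review does not say which dose is right.

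The reply does not remove the contradiction itself. The figure appears in two separate sentences of the legend's prose, so neither the missing image nor one misread character accounts for it, and no other section resolves it.

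**Conclusion.** The article contradicts itself on an injected amount: tenfold per bolus between the CMR scanning text and the Figure 2 legend, and 7.75-fold (1.55 against 0.2 mmol/kg) within the legend. This rests on addition alone and needs no assumption. Only the 0.2075 to 0.215 range depends on one, namely whether the prebolus is counted once or twice.

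The consequence for patients or image reading is conditional on the conflict being present in operational documents, and there is no evidence that any patient received the larger amount. Sample size, power, non-inferiority margin and primary analysis are unaffected. Correction is still warranted, because the figure concerns a dose given to every participant and stands in the text that sets out the imaging sequence. At the time of writing the trial was recruiting, with nine further sites (six German, three UK) being set up.

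**What to change.** 1. Reconcile the CMR scanning section and the Figure 2 legend so that the stress bolus, rest bolus, additional injection and total agree and add up.
2. State whether a prebolus is given at rest and whether the stated total includes the prebolus.
3. Check that the protocol, imaging manual or other instructions used at sites carry the reconciled figures, and notify sites if any do not.

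The choice of dose is for the clinical leads. The cost is a correction to the legend or text and a document check, with a notice to sites if needed. Neither design nor analysis changes.

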### Coronary angiography and pressure wire measurements

At angiography, any arteries with a diameter of > 2.5 mm and a diameter stenosis between 40–99% will be assessed with FFR. A 0.014 guidewire (Radiwire, St. Jude Medical, St. Paul, MN, USA or Volcano, Volcano Corporation, San Diego, CA) will be introduced, calibrated and advanced into the coronary artery distal to the stenosis. An intravenous adenosine infusion (140 mcg/kg/min) will be used to induce maximal hyperaemia. FFR is calculated as the ratio of the mean distal coronary pressure measured by the guidewire to mean aortic pressure measured by the guiding catheter. Revascularisation will be recommended in the FFR group if FFR is < 0.80. In the case of a chronic total occlusion, FFR is regarded as positive and a default value of 0.5 is assigned to the chronically occluded vessel. In the case of triple vessel disease, an attempt should be made to do FFR in all three arteries.

### Investigation reporting

#### CMR analysis

The CMR analysis for the MR-INFORMED group will be done by the local supervising CMR physicianas per normal clinical practice.

The following data will be collected:

1) Image quality (assessed on a grade of 1 to 4 – poor to excellent).

2) Presence of scar tissue and transmurality (1 = 1-25%; 2 = 25-50%; 3 = 51-75%; 4 = > 75%) based on the AHA/ACC 17 segment model.

3) Perfusion analysis at stress and rest scored as significant, insignificant or no defect based on the AHA/ACC 16 segment model (see below).

4) Evidence of regional wall motion abnormalities (1 = akinetic; 2 = hypokinetic; 3 = dyskinetic).

5) Quantitative analysis including end-diastolic and end-systolic volumes and ejection fraction.

The baseline CMR scan in the FFR-INFORMED group will remain blinded.

### Perfusion analysis

The CMR perfusion images will be interpreted visually and angiography recommended if the perfusion defect is classified as significant according to the presence of ischaemia in 2 segments of a 32 segment model (see below) i.e:

• > 60 degrees in either the basal or the midventricular slices or

• > 90 degrees in the apical slice or

• any transmural defect or

• two adjacent slices.

In the case of patients who have unexpected scar tissue evident on CMR, angiography would be recommended for all patients who have evidence of scar and peri-infarct ischaemia. When only scar is present, the management will be decided after an assessment of the transmurality of scar. In patients with transmural scar (> 75%), and no additional ischaemia, angiography would not be recommended. In patients with partial transmurality (< 75%), and no ischaemia, the need for angiography will be decided by the treating physician after an assessment of the patient’s symptoms and risk. It is recommended, however, that the subsequent revascularisation strategy be guided by the areas of ischaemia alone.

The rationale for the threshold at which ischaemia is deemed to be significant is based on data from Hachamovitch et al. [4] who demonstrated that in patients with 10 – 12.5% ischaemic myocardium on SPECT, mortality is significantly higher if they are not revascularised in comparison to a revascularised group. The opposite is true in patients with less than 10% ischaemic myocardium.

With the high spatial resolution of CMR perfusion (< 3 mm x 3 mm) it is possible to distinguish endocardial, non-transmural, perfusion defects from transmural (> 75% wall thickness) perfusion defects. Thus, the myocardium can be divided into the 16 AHA/ACC segments with a subdivision into an endocardial and an epicardial half resulting in a total of 32 segments. Each of these segments represents approximately 3% of the myocardium, two positive segments represent approximately 6%. Since there is no data available providing a direct comparison between the ischaemic burden in SPECT and CMR perfusion this level is used as a conservative threshold to refer patients to invasive angiography.

The criteria for interpretation of CMR scans, especially the differentiation between normal myocardium, non-transmural defects, and transmural defects, will be discussed in detail with each site during the initiation visit using a set of example cases. In addition, CMR images will be periodically reviewed by the global coordinating investigator and selected coordinating investigators from participating countries who – in case of inconsistencies or differences in assessment – will contact the sites and consider specific training activities. Each site can invite a second opinion from the global coordinating investigator or a coordinating investigator from a participating country (or one of their experienced co-workers) in unclear cases.

### Invasive angiography

The results of the coronary angiogram will be assessed by the operator at the time of the angiogram. The following data will be collected:

• Coronary artery dominance

• Location and presence of stenosis by visual estimate

• Vessel diameter

• FFR measurement in all arteries > 2.5 mm with a diameter stenosis greater than 40% but not chronically occludedon visual assessment.

### Revascularisation

Revascularisation by either (PCI) or coronary artery bypass grafting (CABG) will be guided by the ischaemic territories identified by either FFR or CMR perfusion, depending on the randomisation group. For example, if the CMR perfusion scan demonstrates a perfusion defect in the left anterior descending (LAD) territory and angiographically a narrowing is identified in the LAD and right coronary artery (RCA), only the LAD artery will be revascularised.

In visual triple vessel disease, the FFR or CMR results will be used to guide the decision towards CABG or PCI.

If there is more than one artery that needs to be revascularised, the PCI procedure can be staged. If this occurs, follow-up will begin after the first procedure, and the endpoints will include both procedures.

Post-interventional FFR is useful but not mandated in order to keep the procedure as simple as possible.

The specific revascularisation technique, i.e. type of stents used, staging of the procedure, PCI or CABG etc. will be decided by the treating interventionalist and dictated by local guidelines. This is to reflect “real –world” practice and to acknowledge that practice varies between centres and countries. Similarly, the cardiac surgeons will decide on the type of surgical revascularisation that they will undertake.

In the case of patients who demonstrate scar and ischaemia on CMR perfusion subsequent revascularisation will be guided by areas of ischaemia alone rather than on the basis of scar.

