### Endpoints

#### Primary endpoint

The primary endpoint is the occurrence of a Major Adverse Cardiac Event (MACE) at one year. This is a composite end-point of death, myocardial infarction, and repeat target vessel revascularisation. See Table 1 for detailed definitions of endpoints.

**Table 1 T1:** Detailed definition of end-points

**End Point**		**Definition**
Death		All cause mortality
Myocardial Infarction	Spontaneous	Elevation of CK or Troponin above baseline with symptoms of ischaemia, ECG changes or imaging evidence of loss of myocardium [22]
	Peri-procedural	CKMB > 3x ULN - upper limit of normal (post PCI 12-24 hrs) CKMB > 5x ULN (post CABG 24-72 hours) plus new Q waves or LBBB, new native vessel or graft occlusion, imaging evidence of loss of viable myocardium [22]
Repeat revascularisation		Repeat PCI or CABG of the target lesion performed for restenosis or other complication of the target lesion (from 5 mm proximal to 5 mm distal to the stent) [23]

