### Study conduct and randomisation

MR-INFORM is a multi-centre, randomised controlled, non-inferiority trial. It is actively recruiting within the UK, Germany and Portugal. The study is performed in accordance with the principles of the Declaration of Helsinki; with all patients providing informed written consent prior to testing. The study protocol and other relevant documentation have been approved by the South London Ethics Committee (UK) and the relevant national ethics committees as well as registered on ClinicalTrials.gov identifier: NCT01236807: (http://clinicaltrials.gov/ct2/show/NCT01236807?term = MR + INFORM&rank = 1). Suitable patients are identified in the outpatient clinics and from the angiography and CMR waiting lists of the recruiting centres. If they meet the inclusion criteria and none of the exclusion criteria and provide written informed consent, they are enrolled into the study.

Patients are electronically randomised prior to the baseline CMR scan via a web-based randomisation service into randomly varying block sizes of 2 and 4, stratified by study site and gender with an allocation ratio 1:1 to MR-INFORMED or FFR- INFORMED (Figure 1).

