### Data analysis

#### Primary analysis

The main objective of this study is to assess whether an “MR-INFORMED” management strategy is non-inferior to an “FFR INFORMED” strategy for the clinical management of patients with angina who are at moderate to high risk of CAD. To satisfy this objective the study will test the following null-hypothesis:

H_0_: The difference in MACE incidence rates between MRI and FFR group is above or equal to δ .

The outcome will be primarily assessed on an intention to treat basis (mITT) and secondarily on a per protocol (PP) analysis. The null hypothesis H_0_ can be rejected and non-inferiority of the MR-guided strategy claimed, if the two-sided 95% confidence interval (CI) for the difference in incidence rates is completely below δ in both the (mITT) and (PP) analysis. A difference of 6%-points was regarded as clinically relevant. Therefore the non-inferiority margin was set to 6%-points.

In addition, absolute and relative frequencies will be given per group. All statistical analyses will be carried out by an independent statistician. A formal interim analysis is not planned in this study.

For all secondary efficacy variables, descriptive statistics (n, mean, standard deviation, median, minimum, and maximum) will be calculated for each quantitative variable. Absolute and relative frequencies will be given for categorical data.

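### For patients with staged PCI, follow-up starts at a post-randomisation procedure; a single origin at randomisation should be stated for everyone

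*Protocol article*

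**What the plan says.** The rule is in the protocol article under Revascularisation. It first says who can be staged: "If there is more than one artery that needs to be revascularised, the PCI procedure can be staged". It then sets the clock: "If this occurs, follow-up will begin after the first procedure, and the endpoints will include both procedures". The section applies to both groups, since revascularisation "will be guided by the ischaemic territories identified by either FFR or CMR perfusion, depending on the randomisation group". The choice to stage belongs to the operator: "staging of the procedure, PCI or CABG etc. will be decided by the treating interventionalist and dictated by local guidelines".

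Three other statements bear on it:

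- Study conduct and randomisation: "Patients are electronically randomised prior to the baseline CMR scan".
- Primary endpoint: "The primary endpoint is the occurrence of a Major Adverse Cardiac Event (MACE) at one year". No starting point for the year is given.
- Primary analysis: "The outcome will be primarily assessed on an intention to treat basis (mITT) and secondarily on a per protocol (PP) analysis". Non-inferiority requires the two-sided 95% interval for the difference in incidence to lie below 6 percentage points in both analyses.

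Baseline and follow-up visits schedules assessments at 6 and 12 months, again without naming an origin. The staging sentence is the only place in the article where a start of follow-up is stated.

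**The concern.** An intention-to-treat comparison of one-year incidence asks what happens in the year after assignment. Here, for one subset, the year is counted from an event that follows assignment, is chosen by an operator, and depends on the treatment received. The interval from randomisation to the first stage then drops out for these patients, and an interval of equal length is added after the first anniversary of randomisation.

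The subset need not be the same in the two arms. In the FFR-INFORMED group, vessels are selected by pressure-wire measurement in arteries above 2.5 mm with a stenosis above 40%. In the MR-INFORMED group they are selected by ischaemic territory on CMR combined with the angiogram. The number of vessels treated, and so the frequency of staging, could differ. The operator must also know the arm, because the arm's own test guides revascularisation. At stake is whether the primary endpoint has one definition for all randomised patients, which matters most if the confidence limit falls close to the margin.

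**Working it through.** **1. Order of events.** Randomisation precedes the baseline CMR, which precedes angiography and any PCI. The first stage of a staged PCI is therefore always after randomisation.

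**2. What the sentence exposes, read literally.**

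- Non-fatal MI between randomisation and the first stage: outside follow-up.
- Death in that interval: not exposed. The rule applies only where PCI was staged, and a patient who dies before any PCI never enters that subset.
- Peri-procedural MI at the first stage: kept, because the endpoints of both procedures are included.
- Repeat revascularisation of a lesion treated in the trial: cannot occur before the first PCI.
- End of window: one year after the first stage, hence later than one year after randomisation.

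**3. The plan's own sample size.** Inputs from Sample size and Primary analysis: 10% in each arm, margin 6 points, one-sided 0.025 (two-sided 95% interval), 80% power, 1:1.

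- Unpooled variance: n per arm = (1.960 + 0.842)² × 0.18 / 0.06² = 392.4, so 393 per arm, 786 in total.
- Farrington-Manning restricted-null variance: 408 per arm, 816 in total, 1.2% below the stated 826.
- At 413 per arm: SE = √(0.18/413) = 0.02088; 0.06/0.02088 − 1.960 = 0.914; power 82.0%, consistent with at least 80%.
- Dropout: 826/0.90 = 917.8, so 918, as stated.

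The planned size is sound on its assumptions and does not depend on the time origin.

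**4. Illustrative size of the effect.** The article gives neither the share of patients staged nor the risk before the first stage. Both are assumed here. Let s be the staged share in an arm and e the risk of a qualifying event between randomisation and the first stage. Events lost as a proportion of the arm are s × e, and the shift in the MR minus FFR difference is (s_FFR − s_MR) × e. Power is taken at a true rate of 10% in both arms. Type I error is taken at a true difference of 6 points. Both use 413 per arm.

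| s_FFR | s_MR | e | Shift, points | Power | One-sided type I error |
|---|---|---|---|---|---|
| 5% | 5% | 0.5 to 3% | 0 | 82.1 to 82.5% | 2.5% |
| 10% | 5% | 0.5% | +0.03 | 81.8% | 2.4% |
| 10% | 5% | 3% | +0.15 | 80.8% | 2.1% |
| 15% | 5% | 3% | +0.30 | 79.0% | 1.8% |
| 20% | 10% | 3% | +0.30 | 79.6% | 1.8% |
| 5% | 15% | 3% | −0.30 | 86.4% | 3.4% |

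Example, fourth row: 0.15 × 0.03 − 0.05 × 0.03 = 0.0045 − 0.0015 = 0.0030. Power: (0.06 − 0.0030)/0.02060 − 1.960 = 0.808, giving 79.0%. The last row swaps the two shares. At a true difference of 6 points, 0.0030/0.02309 − 1.960 = −1.830, giving 3.4%. More staging in the FFR arm is conservative for the non-inferiority claim; more staging in the MR arm favours it.

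**5. Why these figures lean high.** They count losses only. If the window is a full year moved later, events after the first anniversary of randomisation are gained. Under a constant hazard λ, the risk in any one-year window is 1 − exp(−λ) wherever it starts, so gains offset losses. With a hazard that changes over time the net effect could have either sign. Only non-fatal spontaneous MI can be lost, so the upper end of the range for e is generous.

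**The case against.** The strongest defence is that the sentence has a narrower purpose: to stop a planned second stage from resetting the clock, and to make complications of both stages count. It applies identically to both arms. The article also condenses a longer protocol in which a general origin may be defined. Identical application does stand, and it removes any automatic bias. The narrower purpose is possible, but the sentence does not express it; it states when follow-up begins. A fuller document might add an origin for other patients, but it would still have to be reconciled with this explicit rule.

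A reader might infer more than the text supports:

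- *That the two arms are followed from different origins.* Origins may differ between patients within each arm. They differ between arms only to the extent that staging or delay does.
- *That staged patients are an exception to an origin at randomisation.* No origin is stated for anyone else.
- *That deaths while waiting are lost.* A patient who dies before PCI is never staged.
- *That the sentence contradicts itself on MI at the first stage.* The wording is awkward, but the second clause largely settles that such events count. Peri-procedural MI is in any case ascertained by CKMB 12 to 24 hours after PCI.
- *That the FFR arm goes straight to angiography, so waiting differs by design.* Patient population states that every patient has the baseline CMR.
- *That the bias is about 0.1 to 0.5 points.* That figure comes from a 10% yearly rate over an assumed 4 to 12 week wait (0.10 × 4/52 = 0.8%; 0.10 × 12/52 = 2.3%), multiplied by an assumed staging difference of 10 to 20 points. The 10% includes components that cannot precede the first PCI, the calculation ignores events gained after one year, and neither the wait nor the staging difference is in the document.

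**Conclusion.** The point holds in limited form. The article fixes a post-randomisation, operator-dependent start of follow-up for staged-PCI patients, which does not fit an intention-to-treat comparison of one-year MACE. The literal consequence is that non-fatal MI before the first stage is outside follow-up and the window is displaced for that subset. That such events would actually be excluded is an inference; the text does not say so.

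Bias between arms requires unequal staging or unequal delay, which is plausible but not shown. Its size and direction cannot be computed from the document. With the assumed shares and risks above, and counting losses only, it lies between 0 and 0.30 points in either direction, at most one twentieth of the 6-point margin, and is probably smaller. The planned 826 and 918 are unaffected. This merits correction because it concerns the definition of the primary endpoint, but it does not threaten the trial's validity.

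**What to change.** Replace the staging sentence with a rule covering all patients: follow-up starts at randomisation in both arms, and the primary endpoint is any MACE from randomisation to one year, including peri-procedural events of the first and any later stage. For clarity, restate what Table 1 already implies: a planned second stage on another artery is not a repeat revascularisation, since that component is confined to the target lesion treated for restenosis or another complication. Carry the same wording into the analysis plan.

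The cost is small. The change concerns only how events are counted; it alters no clinical management and needs no extra patients. Randomisation and event dates are needed for every patient. The eCRF very likely holds them, but the article does not say so, and this should be confirmed. With 235 patients recruited at submission out of a planned 918, the rule can be settled before analysis and applied to those already enrolled. The one drawback is that staged patients have slightly less than a year of observation after their first procedure.
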